## Abstract

**Introduction:**

There are no disease-modifying treatments for Parkinson’s disease (PD). We undertook the first drug screen in PD patient tissue and idntified ursodeoxycholic acid (UDCA) as a promising mitochondrial rescue agent. The aims of this trial are to determine safety and tolerability of UDCA in PD at 30 mg/kg, confirm the target engagement of UDCA, apply a novel motion sensor-based approach to quantify disease progression objectively, and estimate the mean effect size and its variance on the change in motor severity.

**Methods and analysis:**

This is a phase II, two-centre, double-blind, randomised, placebo-controlled trial of UDCA at a dose of 30 mg/kg in 30 participants with early PD. Treatment duration is 48 weeks, followed by an 8-week washout phase. Randomisation is 2:1, drug to placebo. Assessments are performed at baseline, week 12, 24, 36, 48 and 56. The primary outcome is safety and tolerability. Secondary outcomes will compare the change between baseline and week 48 using the following three approaches: the Movement Disorders Society Unified Parkinson’s Disease Rating Scale Part 3 in the practically defined ‘OFF’ medication state; confirmation of target engagement, applying ^31^Phosphorus MR Spectroscopy to assess the levels of ATP and relevant metabolites in the brain; and objective quantification of motor impairment, using a validated, motion sensor-based approach. The primary outcome will be reported using descriptive statistics and comparisons between treatment groups. For each secondary outcome, the change from baseline will be summarised within treatment groups using summary statistics and appropriate statistical tests assessing for significant differences. All outcomes will use an intention-to-treat analysis population.

**Ethics and dissemination:**

This trial has been approved by the East of England – Cambridgeshire and Hertfordshire Research Ethics committee. Results will be disseminated in peer-reviewed journals, presentations at scientific meetings and to patients in a lay-summary format.

**Trial registration number:**

NCT03840005.

Strengths and limitations of this studyThis is the first double-blind, randomised, placebo-controlled trial of ursodeoxycholic acid (UDCA) in Parkinson’s disease (PD).This study uses novel secondary outcomes not previously used in a clinical trial studying PD; namely ^31^Phosphorus MR spectroscopy (^31^P-MRS) of disease-specific regions and detailed, complementary home and clinic-based motor activity and gait analysis.^31^P-MRS will allow the assessment of mitochondrial dysfunction directly in the midbrain, including the substantia nigra, the most severely affected brain area in PD.A limitation of the study is the considerable number of capsules patients will have to take; patients will on average be taking an additional nine extra capsules of medication each day through the trial, significantly increasing their ‘pill burden’.A further limitation is the small sample size of n=30 with 20 patients on UDCA and 10 patients on placebo, it will not be possible to draw firm conclusions about the neuroprotective effect of UDCA in PD but will allow for appropriate power and sample size calculations for future studies.

## Introduction

Parkinson’s disease (PD) is a progressive neurodegenerative disorder comprising gait impairment, bradykinesia, rigidity and tremor.^1^ It is the second most common neurodegenerative disorder, predicted to double in global prevalence between 2005 and 2030.^2^ Developing disease-modifying therapies is a crucial step in reducing the associated morbidity of PD and to delay the development of late-stage complications such as dementia, postural instability and psychosis.

Mitochondrial dysfunction is a key pathogenic mechanism in both sporadic and familial PD and therefore a promising target for disease-modifying therapy.^3^ Our group undertook the first drug screen in genetically stratified PD patient tissue.^4 5^ This approach identified ursodeoxycholic acid (UDCA) as a particularly promising mitochondrial rescue compound.^5^ Other groups demonstrated independently the neuroprotective effect of UDCA and its taurine conjugate TUDCA in the 1-methyl-4-phenyl-1,2,3,6-tetrahydropyridine (MPTP) mouse model and the rotenone rat model of PD.^6 7^

The mode of action of UDCA remains to be fully elucidated. Current literature would suggest that it appears to be Akt mediated. Both ursocholanic acid and TUDCA have been demonstrated to induce Akt phosphorylation.^4 7^ Akt activation requires phosphorylation at two sites and promotes cell survival through several mechanisms, failure of activation is a common finding underlying neurodegeneration.^4^ Reduced Akt signalling has been found in in-vitro models of PD and in sporadic PD brains postmortem in the substantia nigra.^8 9^

UDCA has been in clinical use for decades primarily for primary biliary cholangitis (previously primary biliary cirrhosis) with excellent safety and tolerability at the standard dose of 15 mg/kg.^10^ UDCA has also been well tolerated at a higher dose of 30 mg/kg over 2 years in patients with primary sclerosing cholangitis.^11^ UDCA is a naturally occurring bile acid but normally only forms 1%–3% of total endogenous human bile acids. However, in patients on standard therapeutic doses of UDCA (13–15 mg/kg/day), UDCA may form up to 40% of total bile acids. Intestinal absorption after an oral dose is high with a first-pass clearance of about 50%–60%. Plasma levels reach maximum concentrations after 60 min after ingestion with another peak at 3 hours.^12^

A pharmacokinetic study of UDCA in Motor Neurone Disease (MND) demonstrated a significant correlation between serum concentration at 1-hour postdose and CSF concentration 2 hours postdose, with most of the variability in CSF concentrations (78%) explained by variability in serum concentrations. Mean CSF concentration postdose at 15 mg/kg was 86.69 nmol/L, at 30 mg/kg was 114.22 nmol/L and 50 mg/kg was 191.11 nmol/L.^13^

The main objectives of this trial (The UP Study) are to demonstrate the safety and tolerability of UDCA in PD at a dose of 30 mg/kg and to explore the effects of UDCA on novel outcome measures such as ^31^Phosphorus MR spectroscopy (^31^P-MRS) and the objective quantification of motor impairment, using a sensor-based approach. Additionally, we hope to collect an estimate of the effect size and variance of UDCA on the change in motor severity of PD over 1 year compared with placebo using long-established clinical assessment tools.

## Methods and analysis

### Design

This is a phase II, two-centre, double-blind, randomised, placebo-controlled trial of 30 mg/kg of UDCA in early PD. Treatment duration with drug or placebo is 48 weeks in total, followed by an 8-week washout phase. Thirty participants will be included. Randomisation is 2:1 in favour of drug to placebo. The choice of 30 mg/kg day has been informed by previous pharmacokinetic studies in MND, this dose allows effective penetrance of the central nervous system but also balances the exposure to a potentially higher risk of side effects with increasing doses and possible issues with compliance due to the then very large number of additional tablets the patients would need to take.^13^

### Participants

Patients with early PD, as defined by a clinical diagnosis made by a movement disorders specialist according to the Queen Square Brain Bank Criteria within 3 years prior to recruitment and who demonstrate a clear subjective response to dopaminergic medication, confirmed by the treating physician, will be recruited from two sites; Sheffield Teaching Hospitals National Health Service (NHS) Trust (STH) and University College London Hospitals NHS Foundation Trust (UCLH). Key inclusion and exclusion criteria can be found in box 1.^14^

Box 1Key inclusion and exclusion criteria for the UP studyKey inclusion criteriaDiagnosis of Parkinson’s disease (PD) ≤3 years ago based on Queen Square Brain Bank criteria.^14^Subjective improvement of motor impairment on dopaminergic medication with confirmation by a movement disorders expert.Hoehn and Yahr stage ≤2.5 in the practically defined ‘ON’ medication state.Age 18–75 years of any gender.Able to comply with study protocol and willing to attend necessary study visits.Ability to communicate in English.Ability to take study drug.Key exclusion criteriaDiagnosis or suspicion of other cause of parkinsonism.Known abnormality on CT or MRI brain imaging considered likely to compromise compliance with ^31^Phosphorus MR Spectroscopy acquisition.Known claustrophobia or other reasons why patient could not tolerate or be suitable for MRI.Current or previous exposure to ursodeoxycholic acid.Current or previous diagnosis of liver disease (including biliary obstruction), in particular primary biliary cirrhosis judged to be significant.Prior intracerebral surgical intervention for PD (including deep-brain stimulation).Already actively participating in a trial of a device, drug or surgical treatment for PD.Participants who lack the capacity to give informed consent.History of alcoholism.Women of childbearing potential or pregnancy.Concurrent severe depression defined by a score >16 on the Montgomery-Asberg Depression Rating Scale.Concurrent dementia defined by a score lower than 25 on the Montreal Cognitive Assessment.Any medical or psychiatric condition which in the investigator’s opinion compromises the potential participant’s ability to participate.Serum transaminases more than two times upper limit of normal.Patients on ciclosporin, nitrendipine or dapsone.Participants with previous or current diagnosis of inflammatory bowel disease.

Participants are typically recruited through specialist movement disorders clinics at both trial sites. The trial has also been advertised online by the Parkinson’s UK website, the Cure Parkinson’s Trust, the Sheffield National Institute for Health-Related Research (NIHR)-Biomedical Research Centre website and the NIHR Clinical Research Network websites. Trial advertisements direct participants to contact the STH study team to be provided with a patient information sheet and a reply slip to confirm ongoing interest and to organise a pre-screening telephone call to confirm eligibility and suitability for the study.

Study visits either take place at the clinical research facility (CRF) of the Royal Hallamshire Hospital, Sheffield, for STH participants or at the Leonard Wolfson Experimental Neurology Centre, [name] for UCLH participants.

### Primary outcome

The primary outcome for the UP study is to compare the safety and tolerability of UDCA at 30 mg/kg in PD compared with placebo as indicated by the following: the number of serious adverse events (SAEs), number of adverse treatment reactions and the number of patients completing the study. The safety and tolerability of UDCA in this study will be compared descriptively with the reported safety and tolerability of exenatide in the exenatide-PD trial, which followed a broadly similar trial design.^15^

### Secondary outcomes

The effect of UDCA versus placebo will be assessed as a change from baseline to week 48 for the following secondary outcomes:

Clinical assessment using the Movement Disorders Society Unified Parkinson’s Disease Rating Scale (MDS-UPDRS) Part 3 motor examination in the practically-defined ‘OFF’ medication state.In vivo measures of high and low energy metabolite levels (including adenosine triphosphate (ATP), phosphocreatine (PCr) and inorganic phosphate (Pi)) derived from multi-voxel brain ^31^P-MRS at baseline and week 48.Sensor-based, objective quantification of motor impairment using data collected with wearable sensors both in supervised (OptoGait and Opals systems, Sheffield patients only, Dynaport Movemonitor+, all patients) as well as in unsupervised real-life conditions (Dynaport Movemonitor+, all patients).

### Screening visit

Participants likely to be eligible will be invited for a screening visit where all inclusion and exclusion criteria will be reviewed. Participants will be offered the opportunity to discuss the trial and have all questions answered after which they will be asked to provide written informed consent before proceeding to further assessment. Participants will have a full demographic, medical and concomitant medication history taken and reviewed. A physical examination to confirm the diagnosis of PD and exclude PD ‘mimic’ conditions will be performed. A Montreal Cognitive Assessment (MoCA) and Montgomery-Asberg Depression Rating Scale (MADRS) will be performed to exclude concurrent dementia or severe active depression.^16 17^ Safety bloods (full blood count, urea and electrolytes, liver function tests, blood glucose, Haemoglobin A1C (HbA1C), lipid profile) and an ECG will be performed at the screening visit. If the participant remains eligible, they will be provided with an activity monitor (McRoberts, Dynaport MoveMonitor+) to wear for 1 week prior to the baseline visit as described later. For those undergoing ^31^P-MRS, this will be arranged within 1 week before or on the day of the baseline visit, as described later. The baseline visit will be completed within 8 weeks of screening.

### Baseline visit, randomisation and blinding

Randomisation to either active compound or placebo will be administered using a centralised, web-based system hosted by epiGenesys (a wholly owned subsidiary of the University of Sheffield) on behalf of the University of Sheffield Clinical Trials Research Unit (CTRU).

MDS-UPDRS part 3 Motor Examination is performed in the ‘OFF’ state.^18^ The practically defined ‘OFF’ state in this study requires participants to not have taken medication for 8 hours in the case of any drug containing Levodopa, or at least 36 hours in the case of longer-acting agents such as dopamine agonists or enzyme inhibitors.

The supervised gait analysis is performed using a combination of an instrumented photoelectric walkway system (Microgate, OptoGait) and inertial sensors (APDM, Opal) system as described below.

Participants will then be invited to take their usual dopaminergic medication and after a minimum of 60 min undergo the following procedures to reassess them in the practically defined 'ON' state: MDS-UPDRS Parts 1–4 I in the ‘ON’ state, Non-Motor Symptom Questionnaire (NMS-QUEST) and The 39-Item Parkinson’s Disease Questionnaire (PDQ-39).^18–20^

### Intervention

All study medication is provided as a white powder in a hard clear gelatine capsule. Placebo and study drug are completely matched with no identifiable differences in taste, appearance or smell. All packaging and labelling is identical. Each capsule of the active drug contains 250 mg of UDCA.

Treatment with UDCA is started at a dose of 250 mg (one capsule) per day with an increase by 250 mg every 3 days until the target dose is reached, which is divided into three doses.^21^ Most patients are expected to reach their target dose within 3–4 weeks and be on 9–10 capsules per day.

All participants, trial management and medical staff will be blinded to treatment. Participants undergo clinical assessments by the same blinded assessor at each site who is not involved with safety, AE monitoring or dose titration to avoid any assessment bias or accidental unblinding.

### Assessment procedures

Following randomisation and baseline visit, a total of five further visits will be completed at week 12, 24, 36, 48 and 56. At week 48, treatment is completed and all medication returned. A final visit at week 56 for final safety monitoring and outcome measurement completes the study. Week 12 and 36 visits are purely for safety monitoring and medication supply.

The MDS-UPDRS part 3 is completed in the practically defined ‘ON’ state at week 24 and in the ‘OFF’ state at week 48 and 56. The complete MDS-UPDRS (Parts 1–4) is completed in the ‘ON’ state at week 48 and 56.

The ^31^P-MRS is repeated in the 7 days prior to week 48 for UCLH participants and on the day of the week 48 visit for STH participants. The week-long unsupervised at-home physical activity monitoring (PAM) is repeated in the 7 days prior to week 48.

The MoCA, NMS-QUEST, PDQ-39 and MADRS are repeated at week 48 and 56.

At each visit, safety bloods (full blood count, urea and electrolytes, liver function tests, blood glucose, HbA1C, lipid profile) will be obtained. In addition, at each visit a 20 mL serum sample is taken for long-term storage and future research. At the baseline visit, blood is taken for genetic analysis, this will be performed using the NeuroChip Assay that assesses for approximately 180 000 genetic variants associated with neurological diseases.^22^

A full schedule of activities can be seen in table 1.

**Table 1 T1:** Schedule of activities for the UP study

	Procedure	Screening	Baseline	Week 12	Week 24	Week 36	Week 48	Week 56
Medical history	Consent	X						
	Review inclusion/exclusion criteria	X	X					
	Demographics	X						
	Medical history and physical examination	X						
	Height and weight	X					X	
	Genetics Sample		X					
Medication	Randomisation		X					
	Medication supply		X	X	X	X		
	Concomitant medication review	X	X	X	X	X	X	X
	Compliance review			X	X	X	X	
Clinical assessment/outcome measures	MDS-UPDRS Part 3 ‘OFF’		X				X	X
	MDS-UPDRS Part 3 ‘ON’				X			
	MDS-UPDRS Parts 1–4 ‘ON’		X				X	X
	MoCA, MADRS	X					X	X
	PDQ-39		X				X	X
	NMS-QUEST		X				X	
Sensor-based analysis	Dynaport Move Monitor +7 days recording	X					X (7 days prior)	
	OptoGait/Opals gait assessment ‘OFF’		X				X	
MRI	^31^P-MRS		X				X	
Safety monitoring	Safety bloods	X	X	X	X	X	X	X
	ECG	X			X			
	AE review		X	X	X	X	X	X

AE, adverse event; MADRS, Montgomery-Asberg Depression Rating Scale; MDS-UPDRS, Movement Disorders Society Unified Parkinson’s Disease Rating Scale; MoCA, Montreal Cognitive Assessment; NMS-QUEST, Non-Motor Symptom Questionnaire; PDQ-39, 39-Item Parkinson’s Disease Questionnaire; ^31^P-MRS, ^31^Phosphorus MR spectroscopy.

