**Figure 2 F2:**
[figure not shown]
The substantia nigra slice is placed to cover the midbrain with the highlighted voxels of interest for subsequent analyses highlighted in yellow in the sagittal (A) and axial planes (B). Placement of ^31^P-MRS slices. The basal ganglia slice is placed over the putamen aligned in both the coronal (C) axial planes (D), and voxels of interest for subsequent analyses are highlighted in yellow. One voxel covers the anterior putamen and another the posterior putamen.

Details of the acquisition sequences are shown in table 2. Spectra will be processed in the time domain using jMRUI software V.5.2 (http://www.jmrui.eu) and the Advanced Method for Accurate, Robust and Efficient Spectral fitting (AMARES) algorithm is used to determine the relative area under each peak.^33–35^ Analysis of the ^31^P-MRS data will focus on the change between randomisation and week 48 of normalised amplitudes of ATP, PCr and Pi, and ratio values such as PCr/ATP and Pi/ATP that assess bioenergetic dysfunction. All STH patients will undergo ^31^P-MRS. UCLH patients are also invited to attend the STH site for ^31^P-MRS.

**Table 2 T2:** Detailed parameters of the ^31^P protocol for acquisition

Sequence description	Localisation	Decoupling, NOE	TR (ms)	TE (ms)	NSA	Acquired voxel size (mm)	Reconstruction matrix	Reconstructed voxel size (mm)	Scan duration (min)
^31^P-Basal Ganglia	^31^P 2D CSI ISIS localisation	On	4000	0.22	10	40×40×20	12×12	17.5×17.5×20	12:48
^31^P-Substantia Nigra	^31^P 2D CSI ISIS localisation	On	4000	0.22	8	40×40×20	14×14	15×15×20	10:16

CSI, chemical shift imaging; ISIS, image-selected in vivo spectroscopy; NOE, nuclear overhauser efect; NSA, number of signal averages; TE, time to echo; TR, time to repetition.

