### Gait analysis and activity monitoring

Physical activity and gait capacity will be assessed at two time points, namely prior to/during the baseline visit and prior to/during the week 48 visit at the end of the treatment period.

Physical activity will be assessed using home-based ‘real-life’ monitoring for seven consecutive days. A lightweight PAM containing a triaxial accelerometer, gyroscope, digital memory card and a battery (McRoberts, Dynaport Movemonitor+Netherlands) has been selected for continuous monitoring in all participants. Participants will wear the device for seven consecutive days and complete a diary to quantify their physical activity and gait characteristics within their normal weekly routine in a ‘real-world’ setting.

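### At week 48 the London participants' brain scan in Sheffield is scheduled in exactly the seven days of the home activity recording: avoidable noise, cheaply removed

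*Protocol article*

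**What the plan says.** All references are to the protocol article.

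- **Week 48, recording.** Assessment procedures: "The week-long unsupervised at-home physical activity monitoring (PAM) is repeated in the 7 days prior to week 48". This applies at both sites.
- **Week 48, scan.** The same section says of the scan that it "is repeated in the 7 days prior to week 48 for UCLH participants and on the day of the week 48 visit for STH participants".
- **Baseline, recording.** Screening visit: the monitor is handed out "to wear for 1 week prior to the baseline visit as described later".
- **Baseline, scan.** The same section says of the scan that "this will be arranged within 1 week before or on the day of the baseline visit". It does not distinguish the sites.
- **Length and purpose of the recording.** Gait analysis and activity monitoring: "Participants will wear the device for seven consecutive days and complete a diary to quantify their physical activity and gait characteristics", and this is to be done "within their normal weekly routine in a ‘real-world’ setting".
- **Where the scan takes place.** The section on 31P-MRS says "UCLH patients are also invited to attend the STH site for" the scan. Under Participants, the study visits of UCLH participants are in London.
- **Use of the data.** Under Secondary outcomes, the unsupervised recording contributes to a secondary outcome in all participants, analysed as change from baseline to week 48. The Sample size section says that secondary outcome data are to supply effect sizes and variances for planning phase III, and that no longitudinal trial data yet exist for the sensor approach.

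**The concern.** The recording is meant to represent an ordinary week, and it fills its whole window of seven consecutive days. For UCLH participants the week 48 scan has no permitted day outside that window. A participant who accepts the scan must therefore travel between the two cities and attend a scanning appointment in a week that is then analysed as typical.

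The scan rules also differ by site at week 48 but not at baseline. Whether a scan day falls in the first recording, the second, both or neither thus depends on site, on uptake of the scan and on local scheduling. None of these reflects the disease or the drug.

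At stake is the precision of the only home-based sensor measure, and the usefulness of its variance estimate for a later trial. The article states both windows expressly, so this is a collision in the stated schedule and not a detail left out of a condensed text.

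**Working it through.** No sample size, power or error rate enters, and the article gives no figure to reproduce. The check counts calendar days.

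**Convention.** The visit is day 0. Seven consecutive days before the visit are days -7 to -1.

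**Step 1: permitted scan days that fall inside the recording**

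| Time point and site | Permitted scan days | Recording days | Inside the recording |
|---|---|---|---|
| Week 48, UCLH | -7 to -1 (7 days) | -7 to -1 | 7 of 7: unavoidable |
| Week 48, STH | 0 (1 day) | -7 to -1 | 0 of 1: impossible |
| Baseline, both sites | -7 to 0 (8 days) | -7 to -1 | 7 of 8: permitted |

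The two windows are identical only for UCLH at week 48. At baseline the visit day is also allowed. For a UCLH participant that would mean a visit in London and a scan in Sheffield on one day, which the text permits but which is unlikely.

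**Step 2: share of the recording.** One day is 24/168 h = 1/7 = 14.3%. This is an upper bound for a one-day trip, because it counts the whole day as atypical. The two phosphorus sequences last 12:48 and 10:16 minutes (Table 2), together 23:04, plus structural imaging and attendance. An overnight stay, of which the article says nothing, would touch two days (2/7 = 28.6%).

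**Step 3: what reaches the change score.** Let d be the relative departure from usual activity on an affected day, taken as equal at both time points. Let k0 and k1 be 1 if a scan day falls in the baseline or week 48 recording, and 0 otherwise. For a 7-day mean, the shift in the change is d × (k1 - k0)/7.

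| Participant | k0 | k1 | Shift in change |
|---|---|---|---|
| UCLH, scanned in the baseline recording week | 1 | 1 | 0 |
| UCLH, scanned on the baseline visit day | 0 | 1 | +d/7 |
| STH, scanned in the baseline recording week | 1 | 0 | -d/7 |
| STH, scanned on the baseline visit day | 0 | 0 | 0 |
| UCLH, not scanned | 0 | 0 | 0 |

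If the departures differ between the two trips, the first row becomes (d1 - d0)/7. The two days then cancel in part and leave noise.

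**Step 4: illustration.** The article gives no value for d. Assuming 30% to 50% in either direction, one travel day moves a 7-day mean by 0.30/7 = 4.3% to 0.50/7 = 7.1%. This range is for a travel day. It should not be carried over to an STH participant, who is scanned at the home centre.

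**The case against.** **Most of it cancels.** The outcome is a within-person change, and a scanned UCLH participant very probably has a similar trip in the baseline recording week. This stands, and it limits the effect in exactly the group where the overlap is compulsory. Differences between the two trips remain.

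**The Sheffield asymmetry is only permitted.** The two baseline options may have been meant for the two sites, with UCLH scanned in the week before and STH on the day. Table 1 lists the scan under Baseline and the monitor under Screening, which fits. This stands too: the text allows an earlier STH scan but does not show that one is intended. A reader might infer that Sheffield participants acquire a false change as large as a full travel day. The documents do not support this, because no inter-city journey is involved.

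**Bias between arms.** A reader might infer that the treatment comparison is distorted. It is not distorted systematically: scan timing follows site and uptake, and allocation is randomised and blinded. A chance imbalance is possible with 20 and 10 participants.

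**Interrupted recording.** A reader might also infer that the monitor has to come off for the scan. The article does not say so, and the point does not need it.

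**The measure.** The recording also yields gait characteristics, which one unusual day need not shift by anything like 1/7. This stands; the arithmetic applies to averages of activity over the week.

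**Rules elsewhere.** Handling of unusual days may be set out in the full protocol or the analysis plan, neither of which is shown, so no missing rule is alleged. Such a rule could drop the day, but it could not restore seven consecutive ordinary days.

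**Closeness to the visit.** Keeping both measurements near the visit ties them to one time point. That is a genuine reason for the present windows and is the price of changing them.

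**Conclusion.** The point holds as a minor scheduling fault. For UCLH participants scanned at week 48 the overlap is certain under the stated rules. At baseline it is permitted on 7 of 8 days at both sites, and for STH participants at week 48 it cannot occur.

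The affected share is at most 1/7 of a recording for a one-day trip. The net effect on the change from baseline is smaller where both recordings contain such a day. Its actual size is unknown: the article gives neither the number of UCLH participants scanned, who are only invited, nor how far activity on a scan day departs from usual.

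The consequence is avoidable noise and a possible site-by-time artefact in a secondary outcome that is not formally powered but whose variance is meant to inform phase III. The conclusion assumes that the recording occupies days -7 to -1 and that the London visit and the Sheffield scan are separate journeys, as the stated locations imply.

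**What to change.** Schedule scans outside the seven recording days, in the same order at baseline and at week 48:

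- **STH participants:** scan on the visit day at both time points.
- **UCLH participants:** widen the scan window before the visit and start the recording after the scan. For example, scan on days -14 to -8 and record on days -7 to -1. At baseline there is room for this, since up to 8 weeks are allowed between screening and the baseline visit.
- **Where an overlap cannot be avoided:** mark the scan or travel day in the diary that participants already keep, and exclude that day from the activity summary by a rule fixed before unblinding.

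The change is to scheduling wording only and needs no new procedure. The cost is that a UCLH scan may lie up to 14 days from the visit instead of 7, about a week further, or that six days instead of seven are analysed in some participants.

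### The seven-day home activity recording runs into the medication withdrawal needed for the OFF-state visits, so part of each recording is not normal routine

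*Protocol article*

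**What the plan says.** All places are in the Protocol article.

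- **Length and aim of the recording** (Gait analysis and activity monitoring): "Participants will wear the device for seven consecutive days and complete a diary". The aim is to "quantify their physical activity and gait characteristics within their normal weekly routine".
- **Timing at week 48** (Assessment procedures): "The week-long unsupervised at-home physical activity monitoring (PAM) is repeated in the 7 days prior to week 48". Table 1 agrees.
- **Timing at baseline** (Screening visit): the monitor is handed out "to wear for 1 week prior to the baseline visit".
- **OFF preparation** (Baseline visit, randomisation and blinding): the interval without medication is 8 hours for levodopa; for other drugs it is "at least 36 hours in the case of longer-acting agents such as dopamine agonists or enzyme inhibitors". At baseline, usual medication is taken only after the OFF assessments.
- **OFF examination after baseline** (Assessment procedures): MDS-UPDRS Part 3 is done "in the ‘OFF’ state at week 48 and 56". Table 1 also lists an OFF gait assessment at baseline and week 48.
- **Role of the measure** (Secondary outcomes): the home recording belongs to a secondary outcome, change from baseline to week 48, and is collected in all patients.

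No section separates the wear week from the withdrawal period or says that withdrawal hours are set aside.

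**The concern.** The protocol fixes two timings that collide. One puts the home recording directly before the visit. The other has participants stop dopaminergic medication for a set time before the same visit. Hours spent off usual medication because of a trial visit are not part of a participant's ordinary week, yet they enter a measure meant to describe it.

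The exposed share depends on drug class. Participants with the same underlying mobility can therefore contribute different amounts of withdrawal time, and a participant who starts or stops a longer-acting agent between the two recordings changes exposure. The Sample size section says that no longitudinal trial data exist for the sensor approach and that this trial should supply effect size and variance for phase III planning. Avoidable variation in the measure works against that use.

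**Working it through.** The plan gives no figure for this overlap, so there is none to reproduce.

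**Inputs from the Protocol article**
- Recording length: 7 × 24 = 168 h.
- Gap between the end of recording and the visit: none stated. Seven days of wear placed in the seven days before the visit leave 0 h.
- Withdrawal: 8 h for levodopa; at least 36 h for longer-acting agents.

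**Share of the recording in withdrawal** = withdrawal hours / 168
- Levodopa only: 8/168 = 4.8%.
- Longer-acting agents: 36/168 = 21.4%. The 36 h is a minimum, so this share is too.
- Both: if the rule applies drug by drug, the last 36 h split into 36 − 8 = 28 h off the longer-acting agent alone (partial withdrawal) and 8 h off both.
- Difference between the classes: (36 − 8)/168 = 16.7 percentage points. This is the shift when a levodopa-only participant starts a longer-acting agent between visits, or the reverse.

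**Waking time.** Assumption: awake 07:00 to 23:00, so 16 × 7 = 112 waking hours a week.

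| Visit time (assumed) | Waking hours within 8 h | Share of 112 h | Waking hours within 36 h | Share of 112 h |
|---|---|---|---|---|
| 09:00 | 2 | 1.8% | 20 | 17.9% |
| 11:00 | 4 | 3.6% | 20 | 17.9% |
| 13:00 | 6 | 5.4% | 22 | 19.6% |

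For levodopa-only participants with a morning visit, much of the overlap is overnight. For the others, waking time is affected nearly as much as clock time.

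**Possible effect on one recording.** The documents do not say how far activity falls in withdrawal. Assume a fall *d* of 10% to 50% and activity spread evenly over the record. Fall in the weekly mean = share × *d*:
- 8 h: 0.048 × 0.10 = 0.5%, to 0.048 × 0.50 = 2.4%.
- 36 h: 0.214 × 0.10 = 2.1%, to 0.214 × 0.50 = 10.7%.

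**Effect on change from baseline, same assumptions**
- Drug class unchanged: both recordings are multiplied by the same factor, 1 − share × *d*. The change shrinks by that factor (0.893 to 0.979 in the 36 h case). This is dilution.
- Drug class changed: an artificial step of 0.167 × *d*, that is 1.7% to 8.3% of the weekly mean, enters the change score.

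**Hours left if withdrawal time is excluded**
- Longer-acting agents: 168 − 36 = 132 h = 5.5 days.
- Levodopa only: 168 − 8 = 160 h = 6.7 days.

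**The case against.** **The article is condensed.** It gives no clock time for putting on or removing the device, and the full protocol or analysis plan, not shown, may set one or may exclude hours using the diary. This stands as a limit on certainty. It does not remove the point, because the collection window is itself stated, and as stated it runs up to the visit.

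**Most of the week is unaffected.** Even at the 36-hour minimum, 5.5 of 7 days lie outside withdrawal. The number of participants on longer-acting agents is unknown, and for those also on levodopa most of the interval is partial withdrawal. All of this stands and keeps the point small.

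**The percentages are clock time, not effect.** This is correct. The effect figures above rest on an assumed loss of activity.

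**Stronger readings that the documents do not support**
- A reader might infer bias between the arms. The same rule applies at both time points and in both randomised arms. Differential bias would need drug class to change differently by arm, and nothing in the article shows that. If UDCA did alter the need for medication, that change would affect all seven days, which is a wider matter than the overlap.
- A reader might take 36 hours as a ceiling that applies to everyone. It is a minimum, and only for longer-acting agents.
- A reader might add the travel of UCLH participants to Sheffield for spectroscopy. They are only invited, and a scan can fall in the week before either visit, so a distortion of the change is not shown.

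**Conclusion.** The point holds as a minor design flaw. On the plain reading, about 5% of each recording for levodopa-only participants, and at least 21% for those on longer-acting agents, is taken during withdrawal that the trial imposes, against the stated purpose of the measure. The consequence is mainly dilution plus noise that varies with drug class, in a secondary outcome that the Sample size section says is not formally powered. Individual change scores are distorted where drug class changes between visits.

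This rests on three assumptions: that the recording ends at the visit; that the baseline wear week is the one immediately before the baseline visit, as at week 48; and that OFF assessments come first at week 48, as they do at baseline. The primary outcome is not touched.

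**What to change.** Reconcile the recording window with the OFF preparation. Preferably, schedule the seven wear days to end before each participant's withdrawal starts, with the same rule at baseline and week 48. This keeps seven full days and leaves every medication rule as it is. The cost is one scheduling line and handing out or starting the device somewhat earlier.

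Failing that, have participants log the start of withdrawal in the diary they already keep, and exclude the hours from then on in the analysis of both recordings. This costs analysable time: about 5.5 days remain for users of longer-acting agents and 6.7 for levodopa-only participants. Wear time, and possibly the mix of weekdays and weekend days, would then vary by drug class, so the dependence on drug class is moved rather than removed. That is why rescheduling is the better choice.
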